## Abstract

**Background and objectives:**

The kidney is probably the most crucial target of microvascular damage in diabetes, which can ultimately eventuate end-stage renal disease (ESRD). Hemodialysis is the most usual way of renal replacement therapy in ESRD. Patients receiving hemodialysis are susceptible to many complications like hyperglycemia, inflammation, depression, anxiety, and poor quality of life. So, they are constrained to consume many drugs. Medicinal herbs are used in different cultures as a reliable source of natural remedies. This study aims to determine the efficacy of *Nigella sativa* (NS) oil supplementation on blood glucose, kidney function tests, inflammation, oxidative stress, quality of life, and depression in hemodialysis patients.

**Methods and analysis:**

This double-blind, randomized controlled trial will enroll 46 patients with diabetes mellitus who give hemodialysis thrice a week. Patients who have an inflammatory or infectious disease and who are receiving nonsteroidal anti-inflammatory drugs will be excluded. Patients will be randomized to the treatment and control group, which will be recommended using two soft gels of NS and paraffin oil, respectively. Laboratory tests will be assessed at baseline and end of the study, including fasting blood sugar, glycated albumin, insulin, creatinine, blood urea nitrogen, urea, uric acid, superoxide dismutase, malondialdehyde, total antioxidant capacity, high sensitive C reactive protein, and 24-h urine volume. Also, the kidney disease and quality of life and hospital anxiety and depression scale questionnaires will be evaluated.

**Discussion:**

Previous studies have reported a positive effect of *Nigella sativa* supplementation in chronic kidney disease, but there is no evidence that this plant is safe in hemodialysis patients. The results of this study can be helpful in better control of blood sugar and kidney function and reduce complications in diabetic hemodialysis patients.

**Trial registration:**

Iranian Registry of Clinical Trials . Registered on 31 May 2020

**Supplementary Information:**

The online version contains supplementary material available at 10.1186/s13063-021-05917-y.

## Introduction

Diabetes and chronic kidney disease (CKD) are pervasive diseases of the present century, increasing prevalence. Diabetes is the leading cause of renal failure, which ultimately results in the end stage of renal disease (ESRD) and the onset of dialysis or kidney transplantation [1].

By reducing infectious diseases and prolonging the population’s life, CKD has been the most acute chronic non-communicable disease for life-threatening human beings [2]. The prevalence of CKD in different countries depends on many factors, such as gender, age, and economic status. However, it is estimated that 14% of the world’s population is involved in this disease, and accordingly, its prevalence is rising [3]. The prevalence of RRT in many countries, particularly in the Asian continent, is growing, and by 2030, the number of dialysis patients reaches at least 5.4 million [4].

*Nigella sativa* (NS) is an excellent plant from Ranunculaceae and indigenous to Southwest Asia. This plant is used in Iranian traditional medicine to treat various disorders such as respiratory, gastrointestinal, hepatic, and renal disorders. Many of its therapeutic effects have been proven in previous research [5]. Pharmacological studies have shown anti-diabetic, antioxidant, and anti-inflammatory properties of NS because of this plant’s different chemical components. Among these, compounds can be pointed at thymoquinone and nigellidin [6].

About 50% of patients dependent on dialysis are diagnosed with diabetes [7] and are prescribed insulin. Glycosylation of some tissues such as glomerulus and mesangial cells is a determining factor in the progression and development of renal failure. The common indicators for evaluating glycemic status are fasting blood sugar (FBS), glycated hemoglobin (HbA1c), and 2-h postprandial glucose. In previous studies, the positive effect of NS on the reduction of FBS and HbA1c in patients with diabetes mellitus has been well established [8–10].

There are many biochemical and clinical parameters for the evaluation of renal function. The most common are glomerular filtration rate (GFR), serum creatinine, blood urea nitrogen, uric acid, and urinary analysis. The Kidney Disease: Improving Global Outcomes organization has introduced the GFR index as a valid criterion for diagnosis and classification of renal failure. The rate of blood flow through the kidneys in the unit of time is called GFR. The amount of GFR is associated with age, sex, and body surface. Accurate measurement of GFR is complicated, as the filtration process simultaneously takes over millions of glomeruli. So, to measure it, we have to use the estimation formulas [11]. It has had more than 20 formulas for its estimation, which the most used is the Cockcroft-Gault equation [12].

Uric acid is the final product of purine metabolism during DNA and RNA synthesis. Also, the metabolism of food purine is another source of blood uric acid. This indicator is used as a criterion for kidney function. According to cohort studies with a high population, high serum uric acid is a predictor of all death reasons, especially heart disease in dialysis patients [13]. In addition, another criterion for renal function is urine volume. Low urine volume in hemodialysis patients leads to the accumulation of toxic substances in the body. Also, another complication is the cause of edema. Therefore, increasing urine volume is one of the therapeutic goals in hemodialysis patients. According to the study done on patients with diabetes mellitus with renal failure, consumption of NS oil for 3 weeks could cause a significant increase in urine volume in dialysis patients [1].

Approximately 50% of hemodialysis patients have depression and, about 25% of them suffering from severe depression [14, 15]. Several studies have shown that suicide is more prevalent among dialysis patients with depression, and their life expectancy is one third to one sixth of the normal range. Depression in ESRD patients is associated with more complications and higher mortality. Also, adherence to diet and restriction of recommended fluids was lower in ESRD patients with depression [14]. Considering the impairment of renal filtration, the benefits and risks of antidepressant drugs in ESRD patients are controversial. A scientific documentary on the positive effect of antidepressant drugs (fluoxetine, sertraline, citalopram) was not found in comparison with placebo on quality of life in ESRD patients [14]. As a result, the control and treatment of depression are one of the priorities in hemodialysis patients. The hospital scale of anxiety and depression (HADS) is a self-administered questionnaire used to assess the level of anxiety and depression in patients with physical and mental health problems. The HADS scale was first introduced by Snaith to screen psychiatric disorders in public hospitals [16]. This questionnaire has 14 questions parallel to depression and anxiety in patients. So far, many studies have been conducted on the reliability and validity of this scale in different countries and diseases. Translation of the HADS questionnaire in Persian and its standardization was conducted by Montazeri et al. in 2003 [17].

Quality of life is an important criterion that shows the effectiveness of health care, health level, and a good sense of living. In addition, it predicts the occurrence of mortality and duration of hospitalization in hospitals [18]. ESRD is a chronic limiting condition with many adverse effects on different dimensions of patients’ life [19]. RRT exposes patients to a wide range of physical, psychological, economic, and social problems and affects their quality of life. As there is no definite treatment for ESRD patients, many studies have been investigated to evaluate and improve patients’ quality of life. They have introduced this index as a therapeutic target in these patients [18]. Also, regular monitoring of this index as a clinical criterion has expressed the treatment progression of patients treated with RRT [18]. The kidney disease quality of life questionnaire (KD-QOL) is a complete version of the short form 36 health survey questionnaire (SF-36) for renal patients, as well as a self-administered questionnaire. The questionnaire has eight general dimensions for physical and mental health, as well as ten specific dimensions related to kidney disease [20]. Studies have shown a high level of consistency and internal correlation for this instrument. AH Pakpour et al. in 2011 carried out the reliability and validity of this questionnaire in Iran [19].

As mentioned in previous studies, the positive effect of NS on glycemic control in patients with diabetes mellitus and improving the renal function tests has been proven. However, there is no study about hemodialysis patients. Furthermore, quality of life and depression are the most critical qualitative indexes in hemodialysis patients; in this research, we consider the effect of NS supplementation on these indexes.

The overall aim of this design is to determine the effect of NS oil supplementation on indices of renal function, glycemic indexes, oxidative stress, inflammation, quality of life, and depression in patients with diabetes mellitus undergoing hemodialysis. Moreover, its proprietary objectives include the following: (1) determine the effect of NS oil supplementation on serum FBS, HbA1c, GA, serum insulin, insulin resistance, and the B cell function in patients with diabetes mellitus undergoing hemodialysis; (2) determine the effect of NS oil supplementation on serum levels of urea, creatinine, uric acid, and adequacy of dialysis as well as urine volume in patients with diabetes mellitus undergoing hemodialysis; (3) ascertain the effect of NS oil supplementation on superoxide dismutase (SOD), malondialdehyde (MDA), total antioxidant capacity (TAC), high-sensitivity C-reactive protein (hs-CRP) in patients with diabetes mellitus undergoing hemodialysis; and (4) determine the effect of NS oil supplements on quality of life and depression in patients with diabetes mellitus undergoing hemodialysis.

## Methods

### Study setting

The present study is a randomized clinical trial controlled with placebo and two-blinded groups that conform to standard protocol items: recommendations for interventional trials statement (SPIRIT) 2013. The study will be conducted at Imam Reza Hospital of Tabriz, Iran.

### Participants

In this study, the target population is patients with diabetes mellitus undergoing hemodialysis. The inclusion criteria are:

□ An age ≥ 20 years

□ Body mass index = 18.5–30 kg/m^2^

□ Having type 2 diabetes mellitus

□ Two or three times per week hemodialysis

□ Being on hemodialysis for at least 6 months

□ Ability and willingness to cooperate in the study

The exclusion criteria are:
Having inflammatory or infectious diseasesReceiving steroidal or nonsteroidal anti-inflammatory drugsSmokingUsing NS oil regularlyChanges in treatment methods (dialysis)

The hemodialysis process for all patients will be through capillary dialysis filters of polysulfone and bicarbonate dialysis solution. In case of changes in hemodialysis method or type of dialysis filters, the person will be excluded from the study.

The necessary information for obtaining inclusion and exclusion criteria will be extracted from hospital records, and if needed, the patient will be asked orally. The process of recruitment and randomization is illustrated in Fig. 1.

**Fig. 1 Fig1:**
[figure not shown]
The overview of the study

### Interventions

Following the inclusion criteria, after explaining the objectives and method of the study, patients will be consciously entered into the study. They will be randomly allocated to either the intervention or control group. Patients in the NS oil group will receive two soft gels of NS oil, whereas the control group will receive two soft gels of paraffin oil (each soft gel weights 1 g). Treatment of both groups will last for 12 weeks. The selected dose is based on Kaatabi H [8], one of the best practical and safe interventions of NS oil supplementation in patients with diabetes mellitus. According to the predominant studies, NS oil supplementation in the mentioned dose and the term, but even in more prolonged use, did not have certain complications. Just in some rare cases, mild and temporary nausea and dyspepsia and decreased appetite have been reported [9, 10, 21]. The pharmaceutical company will prepare soft gels in a completely similar way in terms of shape, color, and odor. The preparation of black seed oil will be done by the cold press method by the pharmaceutical specialist.

The supplements will be available to attendees every two weeks. All patients will be asked about their usual dietary habits, physical activities, and drug regimens and report any possible changes. In addition, every 2 weeks, all patients will be evaluated by interview. Furthermore, the researcher will give participants a call number to inform him if there are any side effects or other problems Table 1.

**Table 1 Tab1:**
[figure not shown]
Timetable of planned activities during the study directly related to participants

Standard Protocol Items: Recommendations for Interventional Trials (SPIRIT). Schedule of enrolment, interventions, and assessments. *Abbreviations*: NS, *Nigella sativa*; KDQOL, Kidney Disease Quality of Life; HADS, Hospital Anxiety and Depression Scale

### Outcomes measures

Patients will be asked to obtain Informed consent. Next to that, everyone’s demographic and anthropometric indices checklist are filled, and a nutritionist will teach general nutritional recommendations. The dietary intake of individuals will be evaluated by the 3-day food registration questionnaire (two week days and one weekend day). Also, before the intervention, patients will be paid to complete their standard questionnaires, including KD-QOL and HADS, to assess the quality of life, depression, and anxiety. If the patient is illiterate, the information will be received by interviewing. At baseline and the end of the 12th week, 10 mL of blood will be obtained from each patient after 12 h of fasting. Blood serum will be stored at refrigerator temperature (− 70 °C).

The primary clinical outcome measures for the trial are renal function tests as creatinine, urea, uric acid, urine volume, indices related to blood glucose including FBS, HbA1c, GA, serum insulin, insulin resistance and β cell function, indices related to oxidative stress, and inflammation including SOD, MDA, TAC, and hs-CRP. Secondary outcomes include KDQOL and HADS questionnaires and the amount of energy and macronutrients intake.

The process for assessing the activity of hs-CRP, MDA, SOD, and TAC will be done by Navand assay kit (Navandsalamat, Iran) according to the company package insert instruction. The serum insulin level, HbA1c, and GA will be measured by the enzyme-linked immunosorbent assay (ELISA) method. Biochemistry Solutions will also measure creatinine, urea, uric acid, and FBS.

To determine insulin resistance and β cell function, HOMA-IR and HOMA-B formula will be used, respectively [22].

HOMA-IR=$$ \frac{\  glucose\left(\frac{mg}{dl}\right)\times insulin}{405} $$ HOMA-B =$$ \frac{fasting\ insulin\times 20}{fasting\ glucose-3.5} $$

The reliability of laboratory methods by sending the first ten samples of experiments with two different names to the laboratory expert and investigating the level of agreement between them will be determined. Also, body composition will be evaluated by the bioelectrical impedance analysis (BIA) method.

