### Sample size

The sample size for this trial was calculated based on the primary outcome using the G-power software [23] (procedure of two independent groups) or formula $$ n=\frac{\left({\sigma}_1^2+{\sigma}_2^2\right){\left({Z}_{\frac{\alpha }{2}}+{Z}_{\beta}\right)}^2}{{\left({\mu}_1-{\mu}_2\right)}^2} $$. According to the previous results of NS on renal failure [1], the percentage reduction in creatinine (the primary outcome) is 32.43% in the NS group and 9.84% in the placebo group. By considering an alpha error of 0.05, and the power of 90%, the minimum sample size required for each group is 20 participants, in which with predicting a 15% loss, it will be 23 patients in each group. In total, 46 participants will be recruited in this trial.

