## Discussion

Diabetes and chronic kidney disease are the most common diseases of the present century that have an increasing prevalence. Diabetes is the leading cause of diabetic kidney disease (DKD), leading to ESRD and the onset of dialysis or kidney transplantation [1]. The prevalence of RRT is increasing in many countries, and the number of dialysis patients is estimated to reach at least 5.4 million by 2030 [4]. Since there is no definitive and conventional treatment for ESRD patients, treatment in these patients aims to prevent existing complications and improve their quality of life [24].

*Nigella sativa* is a healing plant with positive effects on renal and blood glucose indices in previous experimental and human studies [1, 10]. Also, positive evidence has been reported about improving memory and quality of life and reducing depression, which are common problems in hemodialysis patients. Despite this, no trial has been done on hemodialysis patients.

Considering the relatively low cost and very low complications of this intervention, if significant results are obtained in this study, it can be used as an adjective therapy in these patients. We designed this study to investigate the effect of *Nigella sativa* oil supplementation on the mentioned indices in hemodialysis patients.

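### Serum creatinine, urea and uric acid cannot by themselves show a change in kidney function in patients on maintenance hemodialysis

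*Protocol article*

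**What the plan says.** - **Outcome label.** Outcomes measures: "The primary clinical outcome measures for the trial are renal function tests as creatinine, urea, uric acid, urine volume". The Introduction says of uric acid: "This indicator is used as a criterion for kidney function". It also presents GFR as the accepted criterion for renal failure, but the outcome list has neither GFR nor a residual clearance.
- **Sizing.** Sample size: "According to the previous results of NS on renal failure [1], the percentage reduction in creatinine (the primary outcome) is 32.43% in the NS group", against 9.84% on placebo.
- **Population.** Participants: "Being on hemodialysis for at least 6 months" and "Two or three times per week hemodialysis". No upper limit on time on dialysis and no minimum urine output is given.
- **Urine.** The abstract's list of tests at baseline and end of study closes with "high sensitive C reactive protein, and 24-h urine volume". No urine urea or creatinine assay is named.
- **Dialysis and intake.** Randomisation is stratified by sessions per week, and a change of method or filter leads to exclusion. Food intake is recorded and body composition is measured by BIA. Energy intake and BMI are adjusted for only if needed. Dialysis adequacy is part of the second objective in the Introduction but is absent from the outcome list.

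**The concern.** In a patient whose blood is cleared mainly by a machine, the serum level of a solute has three determinants: how much the body generates, how much dialysis removes, and how much the kidneys still remove. The protocol labels the resulting level as kidney function.

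Randomisation makes a difference in creatinine attributable to the oil. It does not say by which route the oil acted. Lower protein intake or loss of muscle would lower the serum values with no change in the kidneys, and under the present label that would be reported as a renal benefit. Conversely, a real gain in residual function may barely move serum creatinine if the kidneys supply little of the total clearance. At stake is what the trial may conclude from the outcome on which it is sized.

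**Working it through.** **1. The plan's own figure.** The planned contrast is 32.43 - 9.84 = 22.59 percentage points. With a common SD the printed formula is n = 2 × SD² × (1.96 + 1.2816)² / 22.59². The article gives no SD, so 20 per group cannot be computed forwards. Solved backwards, SD = 22.59 × √(20/2) / 3.2416 = 22.04 points. Then 20 × 1.15 = 23 per group, 46 in total, as stated.

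**2. Model.** At steady state, serum level C is proportional to G / (Kd + Kr), where G is generation, Kd is time-averaged dialysis clearance and Kr is residual kidney clearance. Kd of 5-7 mL/min and Kr of 0, 1 or 3 mL/min are assumptions; the document gives neither.

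**3. Residual clearance needed for a 22.59% fall by the kidney alone.** The new Kr is (Kd + Kr) / (1 - 0.2259) - Kd.

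| Starting Kr | Kd = 5 | Kd = 7 |
|---|---|---|
| 0 | 5/0.7741 - 5 = 1.46 | 7/0.7741 - 7 = 2.04 |
| 1 | 6/0.7741 - 5 = 2.75 | 8/0.7741 - 7 = 3.33 |

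Expressed as the kidneys' share s of total clearance, the required relative rise in Kr is (1/0.7741 - 1)/s = 0.2918/s: about 292% at s = 10%, 146% at 20% and 58% at 50%.

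**4. What a moderate kidney effect does to creatinine.** A 30% gain in Kr lowers creatinine by:
- Kr = 0: nothing.
- Kr 1 to 1.3: 1 - 6/6.3 = 4.8% (Kd = 5); 1 - 8/8.3 = 3.6% (Kd = 7).
- Kr 3 to 3.9: 1 - 8/8.9 = 10.1% (Kd = 5); 1 - 10/10.9 = 8.3% (Kd = 7).

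**5. What a non-kidney effect does.** C is proportional to G, so a 10% fall in generation lowers the level by 10% whatever Kd and Kr are.

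**6. Consequence for power.** Keep SD 22.04 and 20 per group, and suppose only a fraction f of 22.59 points can be reached through the kidney. Power is about Φ(3.2416 × f - 1.96): 68% at f = 0.75, 37% at 0.5 and 12.5% at 0.25. The fractions are illustrative.

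**7. Where the effect size comes from.** The Sample size section attributes it to reference [1], on renal failure. The Introduction, citing the same reference, reports a rise in urine volume among dialysis patients. The Introduction later says there is no study in hemodialysis patients, and the Discussion says: "Despite this, no trial has been done on hemodialysis patients". These statements leave the source population undetermined.

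**8. Urine volume.** Patients with no output may be unable to respond. If 20-60% have none (assumed) and none of them responds, the all-patient mean effect is 80-40% of the effect in the others, of whom about 46 × 0.8 = 37 to 46 × 0.4 = 18 remain.

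**The case against.** Much can be said for the plan. Randomisation, stratification by dialysis frequency and exclusion on a change of method or filter protect the between-group comparison. Urine volume is already a primary outcome, so the kidney is not ignored. Intake and body composition are collected. The second objective speaks of serum levels of the solutes, and the abstract says only that the results can be helpful for control of kidney function. All of this stands. It limits the point to interpretation and to transfer of the effect size, but does not remove it: the outcome section still labels the serum values as renal function tests, and nothing ties their reading to the intake or BIA data.

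A reader might infer more than the documents support:

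- **That the planned effect is a 32.43% fall.** That is the change in one arm; the contrast is 22.59 points.
- **That the oil will lower creatinine by suppressing appetite.** Interventions says that in rare cases "mild and temporary nausea and dyspepsia and decreased appetite have been reported". Rare, mild and temporary symptoms do not establish a sustained fall in generation across an arm.
- **That the effect size comes from patients not on dialysis.** The article contradicts itself on this, so only the lack of an established transfer can be stated.
- **That the urine collection already yields residual clearance.** It yields volume. Clearance also needs urea and creatinine measured in the urine and serum timed to the dialysis interval; the article specifies only a 12-hour fast. Since the article is condensed and its schedule table is not shown, it also cannot be said for certain that no urine assay is planned.

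**Conclusion.** The point holds as a matter of interpretation and should be fixed. In patients on maintenance hemodialysis with no residual output required, a fall in serum creatinine, urea or uric acid does not by itself support a conclusion about kidney function. This rests on mass balance, which is general reasoning rather than a statement in the document, but it agrees with the protocol's own handling of dialysis frequency, filters, intake and BMI.

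The size in step 3 depends on the assumed dialysis clearance and on reading a difference in percentage points as a percentage fall. It shows scale and does not predict the result. A reader might go on to call the creatinine comparison biased or the trial unable to succeed; the documents support neither.

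**What to change.** 1. Describe serum creatinine, urea and uric acid as solute levels, and state that no renal-function claim will rest on them alone.
2. Read any fall together with the intake and BIA data already collected and with dialysis adequacy, which should be added to the outcome list to match the objective.
3. Base kidney-function conclusions on urine volume, analysed in all patients and also in those with urine output at baseline. Fix the definition of baseline output before unblinding.
4. Where 24-h urine is still available and serum can be timed to the dialysis interval, add urine urea and creatinine to obtain residual clearance.
5. Reconcile the statements about the population behind reference [1] and say why its effect size is taken to apply here.

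Items 1, 3 and 5 need only wording or analysis, as does item 2 if dialysis adequacy is already recorded. The cost of item 3 is fewer patients in the residual-output analysis. Item 4 needs extra assays and may be impossible for patients whose baseline urine was not kept: the article describes storage of serum only, and Trial status reports first-stage sampling as nearly complete.

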### Statistical analysis

The collected data will be analyzed by the statistical package for the social sciences (SPSS) version 23 software. Descriptive statistics, including frequency, percentage, and central indices and dispersion, will be done. The Wilcoxon signed-rank test will determine the normal distribution of the data. If data distribution is normal, to compare the serum markers and physical components analysis among the study groups in the pre-intervention stage, independent sample *t*-test, and after the intervention, analysis of covariance (ANOVA) will be used by modulating the baseline values and probable variables. A paired-samples *t*-test will be used to compare data in each study group if the data distribution is normal, compared to the serum markers and physical components analysis before the study, Mann-Whitney test, and the study groups. In that case, Wilcoxon signed-rank test will be used (for both before and after the intervention). In all tests, the *p*-value < 0.05 will be considered significant. Missing data will be removed from the final analysis. The number of dialysis sessions per week and the participants’ blood sugar levels will be matched at the beginning of the study. Other confounding factors such as energy intake, BMI, gender, and age will be adjusted if needed.

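### Fourteen laboratory measures are declared primary and every test is run at 0.05, but the sample size treats creatinine alone as the primary outcome

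*Protocol article*

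**What the plan says.** Three sections of the protocol article bear on this.

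- **Outcomes measures** gives the primary outcomes in the plural: "The primary clinical outcome measures for the trial are renal function tests as creatinine, urea, uric acid, urine volume, indices related to blood glucose". The glycaemic group is "indices related to blood glucose including FBS, HbA1c, GA, serum insulin, insulin resistance and β cell function", and the last group is "indices related to oxidative stress, and inflammation including SOD, MDA, TAC, and hs-CRP". No measure is ranked above another.
- **Sample size** uses the singular: "the percentage reduction in creatinine (the primary outcome) is 32.43% in the NS group and 9.84% in the placebo group". The calculation is made "By considering an alpha error of 0.05, and the power of 90" percent. It arrives at 20 per group, or 23 after 15% loss. No other outcome has a stated power.
- **Statistical analysis** sets one threshold throughout: "In all tests, the *p*-value < 0.05 will be considered significant".

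The Discussion then says what would follow: "if significant results are obtained in this study, it can be used as an adjective therapy in these patients". It does not say which results, or how many.

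**The concern.** A reader cannot tell from this document which test is confirmatory. Under Sample size it is creatinine, tested once at 0.05. Under Outcomes measures it is any or all of 14 tests, each at 0.05. The two readings carry very different risks of a false claim.

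The Discussion ties possible clinical use to significant results without naming an outcome. The Ethics considerations section also makes a later step depend on the supplement being effective, again undefined. Nothing in the text would stop a lone result on, say, MDA or TAC from being presented as a positive primary finding, although the trial was not sized for it.

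**Working it through.** **1. Count of primary outcomes (Outcomes measures).**
- Renal: creatinine, urea, uric acid, urine volume = 4.
- Glycaemic: FBS, HbA1c, GA, insulin, insulin resistance, β cell function = 6.
- Oxidative stress and inflammation: SOD, MDA, TAC, hs-CRP = 4.
- Total: 4 + 6 + 4 = 14.

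**2. The plan's own sample size.** The difference is 32.43 − 9.84 = 22.59 percentage points, with two-sided α = 0.05 and power 90%. No standard deviation (SD) is stated, so n = 20 cannot be reproduced. The SD can only be solved for:
- Normal formula, n = 2·SD²·(1.960 + 1.282)²/22.59². Setting n = 20 gives SD ≈ 22.0.
- Two-sample t-test, n = 20 and power 90%: standardised effect 1.052, so SD ≈ 22.59/1.052 ≈ 21.5.

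The loss step agrees with the text: 20 × 1.15 = 23 per group, 46 in total.

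**3. Chance of at least one false positive among 14 tests at 0.05, when no outcome is affected.**

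| Assumption about the tests | Chance |
|---|---|
| All independent: 1 − 0.95^14 | 51% |
| HOMA-IR and HOMA-B computed from glucose and insulin, rest independent (simulation) | about 48% |
| Same, with correlation 0.3 or 0.5 within each group of measures | about 46% or 42% |
| Common correlation 0.2 among all 14 | about 48% |
| Common correlation 0.3 | 44% |
| Common correlation 0.5 | 35% |
| Common correlation 0.7 | 25% |

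The document gives no correlations, so every row below the first rests on assumed values. The HOMA rows also assume a spread for glucose and insulin. Full independence cannot hold, because Outcomes measures derives the two HOMA indices from glucose and insulin, which are themselves on the list.

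**4. Cost of keeping all 14 as primary under Bonferroni.** Each test would use 0.05/14 = 0.00357. Creatinine power at 20 per arm would be:

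| Back-solved SD | t-test | Normal approximation |
|---|---|---|
| 22.0 | 56% | 63% |
| 21.5 | 59% | 66% |

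With SD 22.0 and the normal formula, restoring 90% power would need about 34 per group, or 34/0.85 = 40 after 15% loss.

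**5. If creatinine alone is primary,** the type I error of the primary claim is 5% and the planned sample size is unaffected.

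**The case against.** **Independence.** It is tempting to say that the false positive rate is about 50%. That requires 14 independent tests, which the HOMA formulas rule out. This objection stands: 51% is an upper figure, not an estimate. Even at a common correlation of 0.7, however, the rate is 25%, five times nominal.

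**Success rule.** A reader might infer that any one of the 14 makes the trial positive. The protocol nowhere says so. Statistical analysis sets a threshold for tests, the Discussion remark is general, and Ethics considerations does not define effective. This also stands. The family-wise figures describe one reading, and on the Sample size reading the error is 5%. But no passage excludes the wider reading, and the plural list of primaries invites it.

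**Condensed article.** A multiplicity procedure may sit in a full protocol or SAP that is not shown, so its absence here is not a finding. That is fair, but the point does not rest on the absence. The article states the primary outcome in two incompatible ways and itself fixes 0.05 for all tests. An unseen adjustment would conflict with that sentence.

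**Power figures.** They depend on an SD that the document does not give. That is why a range is shown.

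**Conclusion.** The point holds as a contradiction in the text. Outcomes measures declares 14 primary outcomes, Sample size declares and powers one, and Statistical analysis tests everything at 0.05.

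If one significant primary measure were accepted as evidence of efficacy, the chance of a false positive would be up to 51% under independence and roughly 35% to 48% under moderate correlation. This is conditional on that reading and on the assumed correlations. Keeping all 14 with Bonferroni would leave creatinine power at roughly 56% to 66%, given an SD of about 21.5 to 22 points back-solved from n = 20. The documents do not support a claim that the trial has a one-of-14 success rule, or that its error rate is simply one half. The conflict should still be resolved before the results are known, because it decides what the trial's main claim is.

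**What to change.** - In Outcomes measures, name creatinine as the single primary outcome, tested at two-sided 0.05.
- State its measure from baseline to week 12, and make it the same in all sections. Sample size used percentage reduction ("is 32.43% in the NS group and 9.84% in the placebo group"), whereas Statistical analysis plans a comparison adjusted for baseline. These are different quantities with different SDs. Simply naming the week-12 level would leave the power calculation mismatched.
- Make the other 13 measures secondary. Either test them under Holm, or report them with confidence intervals and no confirmatory claim. Amend the sentence on the 0.05 threshold to match.
- Base the overall efficacy conclusion in the Discussion on the creatinine test.

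Trial status shows that enrolment began on 1 June 2020 and first-stage sampling was nearly complete. The change therefore needs a dated amendment, with reasons, made before unblinding and carried into the registry entry. It needs no further patients or measurements. The cost is fewer outcomes on which efficacy can be claimed. If the sponsor prefers to keep all 14 as primary, the plan needs a stated multiplicity procedure and a sample size recalculated to suit.
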